## Abstract

**Background:**

Although EGFR-TKIs have substantially improved outcomes in EGFR-mutated advanced NSCLC, acquired resistance ultimately leads to treatment failure in most patients. Yifeixiaoji Decoction (YFXJD), a traditional Chinese herbal formulation, has shown promise as an adjunctive strategy; however, evidence from prospective clinical studies for this specific formula remains limited. We therefore designed this trial to assess whether YFXJD could prolong progression-free survival when added to standard osimertinib therapy in advanced NSCLC.

**Methods:**

A total of 200 patients with stage IV EGFR-mutant NSCLC will be enrolled in a randomized, double-blind, placebo-controlled trial and allocated 1:1 to receive standard osimertinib therapy combined with either YFXJD granules or matched placebo. The primary endpoints is progression-free survival. Key secondary endpoints include change in TCM syndrome score, objective response rate, quality of life (EORTC QLQ-C30/LC13), safety (NCI CTCAE v5.0), and exploratory peripheral blood biomarker analyses.

**Expected results:**

This trial will provide prospective evidence regarding the efficacy and safety of YFXJD as an adjunct to osimertinib therapy in patients with advanced EGFR-mutant NSCLC and will determine whether this approach influences clinical outcomes.

**Clinical trial registration:**

https://itmctr.ccebtcm.org.cn, ITMCTR2025002306.

## Introduction

Epidermal growth factor receptor tyrosine kinase inhibitors (EGFR-TKIs) have substantially improved outcomes for patients with advanced non-small cell lung cancer (NSCLC) harboring sensitizing EGFR mutations, prolonging progression-free survival (PFS) and improving quality of life (1). NSCLC accounts for approximately 85% of all lung cancer cases, which remains the leading cause of cancer-related mortality worldwide (2). Despite these clinical benefits, acquired resistance to EGFR-TKIs develops in nearly all patients, with a median PFS typically ranging from 9 to 13 months for first-generation TKIs (3). Overcoming or delaying resistance has therefore become a major clinical challenge in this population.

Traditional Chinese medicine (TCM) may exert multi-targeted therapeutic effects, including modulation of immune function (4), symptom relief, improvement of quality of life, and potential influence on the tumor microenvironment (5). The CATLA trial, a multicenter randomized double-blind placebo-controlled study, demonstrated that adding Chinese herbal medicine to first-generation EGFR-TKIs (erlotinib, gefitinib, or icotinib) significantly prolonged median PFS from 10.94 to 13.50 months (HR 0.68, 95% CI 0.51–0.90, *p* = 0.0064) (6). The subsequent CATLA-2 protocol is currently evaluating Yiqi-Yangyin-Jiedu Decoction (YYJD) combined with osimertinib as first-line treatment (7). These studies provide important evidence for the potential of TCM as an adjunctive strategy but also highlight the need for formula-specific investigations (8).

Building on these findings and based on our preclinical observations that a combination of *Punica Granatum* Peel and Dioscorea Nipponica inhibited the activation of dormant lung cancer cells and suppressed tumor growth *in vivo* (9), our research team developed Yifeixiaoji Decoction (YFXJD). YFXJD is a multi-herb formulation containing specific components such as Dioscorea nipponica, *Punica granatum* pericarp, and *Houttuynia cordata*, which have demonstrated anti-dormancy and anti-tumor effects in preclinical models. Preliminary clinical observations suggested trends toward enhanced efficacy and reduced toxicity. However, prospective randomized controlled clinical evidence for this specific formula in the current era of uniform osimertinib therapy remains lacking.

To address this gap, we designed a single-center, randomized, double-blind, placebo-controlled clinical trial to evaluate whether adjunctive treatment with YFXJD can prolong PFS and improve clinical outcomes in patients with advanced EGFR-mutant NSCLC receiving standard osimertinib therapy. The study will also assess safety and explore the biological effects of YFXJD, providing evidence to guide the integrated use of Chinese and Western medicine in this patient population.

## Methods and analysis

### Study design

#### Trial design

This is a single-center, randomized, double-blind, placebo-controlled clinical trial with two parallel groups. A total of 200 patients with advanced EGFR-mutant NSCLC will be enrolled and randomly allocated in a 1:1 ratio to either the YFXJD group or the control group receiving placebo. Both groups will receive standard osimertinib therapy (80 mg orally once daily) throughout the study period.

#### Recruitment and informed consent

Participants will be recruited through outpatient and inpatient referrals and study advertisements at Shuguang Hospital, Shanghai University of Traditional Chinese Medicine. Eligible patients will undergo a structured interview during clinic visits or upon admission, during which the study procedures—including treatment duration, imaging schedule, blood sampling, potential risks, and participants’ rights to withdraw at any time—will be explained in detail. Written informed consent will be obtained prior to enrollment.

#### Allocation and intervention

After obtaining informed consent, participants will be randomized to receive either adjunctive YFXJD granules or matched placebo in addition to standard osimertinib therapy. The key components of YFXJD are presented in Table 1. Treatment will continue until predefined discontinuation criteria are met, including disease progression, intolerable adverse events, withdrawal of consent, or completion of the study protocol.

**Table 1 tab1:** Main components of YFXJD.

Chinese name	Latin name	Source plant	Amount (g)
Beishashen	Glehniae Radix	*Glehnia littoralis* F. Schmidt ex Miq.	12
Maidong	Ophiopogonis Radix	*Ophiopogon japonicus* (L. f.) Ker-Gawl.	9
Chuanshanlong	Dioscoreae Nipponicae Rhizoma	*Dioscorea nipponica* Makino	9
Mohanlian	Ecliptae Herba	*Eclipta prostrata* (L.) L.	9
Yuxingcao	Houttuyniae Herba	*Houttuynia cordata* Thunb.	9
Shiliupi	Granati Pericarpium	*Punica granatum* L.	9
Jiegeng	Platycodonis Radix	*Platycodon grandiflorus* (Jacq.) A. DC.	3

#### Follow-up and assessments

Follow-up visits will occur every 3 months, as outlined in Table 2, and will include clinical evaluation, imaging studies, laboratory testing, and assessment of adverse events. Imaging for tumor response assessment will be performed every 8 weeks from randomization until disease progression. The efficacy of YFXJD will be evaluated through progression-free survival, TCM symptom scores, activity levels, biochemical parameters, and exploratory biological indicators. Safety will be assessed according to protocol-defined criteria. The trial flowchart is presented in Figure 1.

**Table 2 tab2:** Schedule of trial.

Assessment/Time point	Screening	Baseline/Initiation	Treatment period	Treatment period	Long-term follow-up	End-of-treatment visit	Survival follow-up
	D -7	D0	D90 ± 7	D180 ± 7	D365 ± 7	Upon PD/Discontinuation	
Procedures							
Informed consent	✓						
Eligibility review	✓						
Data collection							
Demographic information	✓						
History of NSCLC & treatment	✓						
History of other diseases	✓						
Randomization & drug dispensing		✓	✓ (Re-supply)	✓ (Re-supply)			
Primary endpoints							
1. PFS (RECIST 1.1)			Imaging per protocol	Imaging per protocol	Imaging per protocol	✓ (Confirm PD)	Record death
2. TCM Syndrome Score	✓ (Baseline)		✓ (Interim)	✓ (Primary Time Point)			
Secondary endpoints (Efficacy)							
Tumor response (ORR/DCR)			✓	✓	✓	✓ (Final)	
Quality of life (EORTC QLQ)	✓ (Baseline)		✓	✓	✓		
Performance status (KPS)	✓ (Baseline)		✓	✓	✓		
Biomarkers							
Lymphocyte subsets	✓ (Baseline)		✓	✓	✓		
Inflammatory cytokines	✓ (Baseline)		✓	✓	✓		
Tumor markers	✓ (Baseline)		✓	✓	✓		
Safety assessments							
Clinical laboratory tests							
CBC, hepatic & renal function	✓	✓	✓	✓	✓	✓	
Urinalysis & stool routine	✓	✓	✓	✓	✓	✓	
AE/SAE collection	✓	✓	✓	✓	✓	✓	
EGFR-TKIs specific AE recording		✓	✓	✓	✓	✓	
Concomitant medication record		✓	✓	✓	✓		
Proportion with dose Mod./Disc.			Recorded	Recorded	Recorded	✓ (Final)	
Study administration							
Protocol deviation record		✓	✓	✓	✓		
CRF completion		✓	✓	✓	✓	✓	

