#### TCM intervention

The TCM intervention will be administered concurrently with EGFR-TKIs therapy and will continue until disease progression, unacceptable toxicity, or other criteria for treatment discontinuation are met. Both the YFXJD and placebo are manufactured as granules. Each sealed packet contains a fixed dose of granules (10 g per packet, 5:1 extraction ratio), with identical packaging to ensure complete blinding in terms of appearance, texture, smell, and taste. Matching placebo granules with similar appearance, odor, taste, and packaging, without active herbal ingredients. Are composed of pharmaceutical-grade excipients (primarily maltodextrin) with approved food colorants and flavorings.

Quality control of YFXJD granules includes: (1) botanical authentication of all raw herbs with voucher specimens deposited at the Shanghai University of TCM Herbarium; (2) compliance with Chinese Pharmacopoeia 2020 edition standards; (3) chemical fingerprinting by HPLC for batch-to-batch consistency; (4) 12-month stability testing; and (5) testing for pesticides, heavy metals, microbes, and adulterants. The YFXJD granules and placebo are produced under Good Manufacturing Practice (GMP) standards at Sichuan Neo-green Pharmaceutical Technology Development Co., Ltd. The manufacturer supplied the study products but had no role in study design, data collection, analysis, or manuscript preparation; no financial or non-financial competing interest exists.

Patients will be instructed to dissolve the contents of one packet in approximately 150–200 mL of hot water and to take it orally twice daily (morning and evening), 30 min after meals. The daily total dose will therefore consist of two packets. The dosage and administration frequency will remain constant throughout the treatment period unless modified due to tolerability issues as assessed by the investigator.

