##### Herb-drug interaction review

Osimertinib is primarily metabolized by hepatic CYP3A4. The following measures will be implemented: (1) systematic review of all herbal components for potential CYP3A4 interactions; (2) prohibition of concomitant herbal medicines known to interact with CYP3A4 (e.g., St. John’s Wort, Glycyrrhiza, Scutellaria); (3) specific monitoring for overlapping hepatic toxicity (ALT/AST every 4 weeks), gastrointestinal toxicity, and pulmonary toxicity (ILD monitoring); and (4) dose modification guidelines for osimertinib in case of grade ≥3 toxicity.

Participants who experience severe adverse events (AEs) assessed as related to the trial intervention will be provided with necessary post-trial medical care and may receive appropriate compensation in accordance with relevant regulations and the insurance protocol for this clinical trial. For any adverse reactions determined to be unrelated to the study medication, standard medical management will be provided based on a comprehensive assessment of the participant’s condition, including medical history, clinical symptoms, physical signs, and results from laboratory tests, imaging, and other diagnostic examinations.

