### Outcomes

#### Primary outcomes

Progression-Free Survival (PFS): Defined as the time from randomization to the first occurrence of radiographic disease progression according to RECIST 1.1 (15) criteria or death from any cause, whichever occurs first. Imaging will be performed every 8 weeks from randomization until disease progression, with blinded independent central review.

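### Table 2 contradicts the text on liver-test frequency, visit schedule and product supply, and the three need to be reconciled into one schedule

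*Protocol article*

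**What the plan says.** **Visits.** Follow-up and assessments states "Follow-up visits will occur every 3 months, as outlined in Table 2, and will include clinical evaluation, imaging studies". The dated columns of Table 2 are D-7, D0 and then "D90 ± 7 D180 ± 7 D365 ± 7 Upon PD/Discontinuation", followed by an undated survival follow-up column.

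**Liver tests.** Herb-drug interaction review lists, among the measures to be put in place, "specific monitoring for overlapping hepatic toxicity (ALT/AST every 4 weeks". The hepatic function row of Table 2 is ticked at screening, D0, D90, D180, D365 and the end-of-treatment visit, and nowhere else.

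**Product.** TCM intervention says that the granules "will continue until disease progression, unacceptable toxicity, or other criteria for treatment discontinuation are met". Allocation and intervention gives a similar list and adds completion of the study protocol, without a date. Table 2 shows dispensing at D0 and re-supply at D90 and D180. The D365 cell is blank, and that column is headed as long-term follow-up, whereas D90 and D180 are headed as treatment period.

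**Imaging.** Follow-up and assessments and Primary outcomes agree: "Imaging will be performed every 8 weeks from randomization until disease progression". The PFS row of Table 2 refers imaging back to the protocol at each dated visit. The ORR/DCR row is ticked at D90, D180, D365 and end of treatment.

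**The concern.** The text names Table 2 as the schedule, so site staff can be expected to work from it. Where the two disagree, what happens to a patient depends on which one is followed.

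- **Safety.** The 4-weekly liver tests are a stated safeguard against overlapping hepatic toxicity of the herbal product and osimertinib. Someone working from the table would not do them.
- **Treatment contrast.** The trial compares granules with placebo up to progression. If supply ends where the table's marks end, later PFS events occur in patients taking neither, and the arms are pulled together.
- **Adherence.** Adherence monitoring relies on packets returned at each visit, and no dated visit exists after D365.

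Trial status reports enrolment since January 2026, 38 patients enrolled by July 2026 and no amendment. The earliest participants are therefore at or near D180, the last marked re-supply.

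**Working it through.** The article states no figure for this point, so there is none to reproduce. The check compares calendars and then sizes the consequence from the medians in Sample size.

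**1. Liver tests.** Text: one test per 28 days, 365 / 28 = 13.04, so 13 post-baseline tests by D365. Table 2: 3 dated post-baseline tests by D365 (D90, D180, D365), plus one at end of treatment. Longest interval: 365 − 180 = 185 days, against 28.

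**2. Visits.** Text: every 3 months gives 4 visits in the first year. Table 2: 3, with none near D270. Sample size gives 12 months' accrual and at least 12 months' follow-up, so a patient is followed for 12 to 24 months. The period after D365 without a dated visit therefore runs from about 0 months (last enrolled) to about 12 months (first enrolled).

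**3. Supply.** At 2 packets a day, D90 to D180 needs 2 × 90 = 180 packets and D180 to D365 needs 2 × 185 = 370. The table gives no quantity. If the D180 re-supply matches the D90 one, product lasts to about D270. If it is sized for the longer gap, product lasts to about D365. Nothing is marked after that in either case.

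**4. Patients still progression-free.** S(t) = exp(−ln 2 × t / median), medians 18.9 and 28.6 months, one month = 30.44 days, no dropout.

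| Day | Control | YFXJD | Mean × 200 |
|---|---|---|---|
| D180 (5.91 months) | 0.805 | 0.867 | 167 |
| D270 (8.87 months) | 0.722 | 0.807 | 153 |
| D365 (11.99 months) | 0.644 | 0.748 | 139 |

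**5. PFS events after supply would end.** With uniform accrual over a = 12 months and minimum follow-up f = 12 months, the event probability is 1 − [exp(−λf) − exp(−λ(a + f))] / (λa), with λ = ln 2 / median. This gives 0.479 (control) and 0.351 (YFXJD), so 100 × 0.479 + 100 × 0.351 = 83 events. Events by D365: 200 × (1 − 0.696) = 61. Events by D270: 100 × 0.278 + 100 × 0.193 = 47. Events after D365 are thus 83 − 61 = 22 (27% of 83). Events after D270 are 83 − 47 = 36 (43%).

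**6. Imaging (minor).** Eight-weekly scans fall on D56, 112, 168, 224, 280, 336 and 392. The visit windows are D83–97, D173–187 and D358–372. No scan date falls in any of them, so the ORR/DCR ticks do not match the dates on which response can be read.

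**The case against.** A fair defence is that the table shows core visits and the text adds to them: 4-weekly liver tests between visits, with extra visits and supply as needed. The article also condenses a fuller protocol. This explains how the mismatch may have arisen but does not remove it. The PFS row shows how the table refers back to the text where that is meant, and the laboratory and dispensing rows carry no such reference. The visit sentence also says outright that the 3-monthly schedule is the one in Table 2.

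Three stronger readings are tempting, and the documents do not support them.

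- **That Table 2 sets a rival PFS scan interval, delaying detection of progression.** It does not. The PFS row defers to the protocol, and the 8-week rule is stated twice in agreement. What remains is the ORR/DCR row and a loose sentence that lists imaging among visit contents. A detection delay would arise only if scans were tied to visit dates, which the PFS row does not say.
- **That the table stops at D365 and adverse events go uncollected afterwards.** Only dated visits stop. An end-of-treatment visit (progression confirmed, laboratory tests, AE/SAE collection) and survival follow-up come after. The safety paragraph under Secondary outcomes keeps AE surveillance going throughout, and Randomization and blinding requires serious AEs to be reported within 24 hours.
- **That product certainly runs out.** The table gives no quantities, and completion of the study protocol is an undated stopping criterion. The supply point is an unresolved contradiction, and the dilution is conditional on the table being treated as exhaustive.

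**Conclusion.** The contradictions on liver tests, visits and product supply are real and stand on the printed text alone. The liver-test discrepancy is 3 dated post-baseline tests against 13 by D365, and affects a stated safety measure. The visit discrepancy is one missing visit in year one and up to about 12 months without a dated visit. The supply discrepancy leaves treatment duration unclear for the 139 of 200 patients (about 70%) expected to be progression-free at D365.

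If supply did follow the table, about 22 to 36 of 83 expected PFS events would fall after product ended, depending on the quantity given at D180. These figures rest on exponential PFS at the stated medians, uniform 12-month accrual and no dropout. Sample size itself expects about 130 events, which those medians do not reproduce under 12 plus 12 months, so the counts show scale only. The primary endpoint is exposed through continuity of supply and visits. Its scan interval is not in conflict. The ORR/DCR timing is a minor mismatch.

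**What to change.** Reconcile Table 2 with Allocation and intervention, Follow-up and assessments, TCM intervention, Herb-drug interaction review and Primary outcomes, and issue one schedule. It should:

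- show liver tests, visits and product supply for the whole period to which each applies, including any time after D365;
- agree with the text on whether D365 lies within the treatment period, and state what completion of the study protocol means for treatment;
- tie ORR/DCR to the protocol imaging dates instead of D90, D180 and D365.

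Which monitoring interval and treatment duration apply is for the sponsor's clinicians to confirm. This review takes no position on either.

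The cost is a table edit, a few sentences, a site memo and approval of the amendment by the ethics committee, which Ethics and dissemination requires before implementation. It is best done now, because the first participants are reaching the last marked re-supply.

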### Withdrawal/termination criteria

Participants will be withdrawn or terminated from the trial if any of the following conditions are met:Failure to adhere to the key procedures outlined in the study protocol, which may compromise the validity of the data obtained from that participant.The use of concomitant therapies that are prohibited by the protocol for the management of NSCLC or its symptoms.Discontinuation of osimertinib due to toxicity: Occurrence of severe adverse reactions attributable to osimertinib therapy that necessitate the permanent discontinuation of the targeted agent, as determined by the treating physician. This criterion focuses on adverse events (e.g., severe interstitial lung disease, hepatotoxicity, or intolerable grade 3/4 rash or diarrhea) that make continued osimertinib treatment unsafe.Withdrawal of consent: The participant voluntarily decides to withdraw from the study at any time for any reason.Loss to follow-up: The participant becomes unreachable or fails to attend scheduled study visits without providing reason, despite repeated attempts at contact by the research team.The principal investigator determines that continued participation is not in the best interest of the participant’s health and safety.

Participants who are discontinued from the study intervention will be encouraged to continue in the follow-up phase for the collection of survival and safety data, where feasible and with their consent. All reasons for withdrawal or discontinuation will be documented in the case report form.

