#### Secondary outcomes

Change in TCM Qi-Yin Deficiency Syndrome Score: The absolute change in the total score from baseline to 6 months (D180 ± 7), assessed using a pre-specified and validated TCM syndrome scale specific for Qi-Yin deficiency in lung cancer. The scale ranges from 0 to 48, with higher scores indicating more severe symptoms. The minimal clinically important difference (MCID) is 4 points. All TCM assessors will undergo a 2-day training session with standardized patients, and inter-rater reliability (kappa ≥ 0.80) will be established prior to study initiation.Objective Response Rate (ORR) and Disease Control Rate (DCR) as per RECIST 1.1 (15).Duration of Response (DOR).Overall Survival (OS).Change in health-related quality of life assessed using the European Organization for Research and Treatment of Cancer Quality of Life Questionnaire Core 30 (EORTC QLQ-C30) (16) and its lung cancer-specific module (QLQ-LC13) (17).Change in Karnofsky Performance Status (KPS) score (18).Incidence, type, severity, and relationship to study treatment of all Adverse Events (AEs) and Serious Adverse Events (SAEs), graded according to the National Cancer Institute Common Terminology Criteria for Adverse Events (NCI CTCAE) Version 5.0 (19).

Evaluation of EGFR-TKIs-related specific adverse reactions:Rash: A validated skin toxicity assessment tool (e.g., HFSR-14 scale or specialized assessment based on CTCAE v5.0 dermatology criteria) will be used to record the incidence, maximum severity (grade), time to onset, duration, and management measures (e.g., topical/systemic medications, dose modifications) of rash.Diarrhea: The incidence, maximum severity (graded per CTCAE v5.0 gastrointestinal criteria), duration, frequency of diarrhea will be recorded, along with the proportion of patients requiring EGFR-TKIs dose modification, interruption, or discontinuation due to diarrhea. The use of anti-diarrheal medications will also be documented.The proportion of patients requiring EGFR-TKIs dose reduction, interruption, or permanent discontinuation due to the above or any other AEs.Changes in serum levels of inflammatory cytokines (IL-2, IL-6, IL-10, TNF-*α*, IFN-*γ*).Changes in peripheral blood lymphocyte subsets (CD3^+^, CD4^+^, CD8^+^, CD4^+^/CD8^+^ ratio, NK cells).Changes in serum tumor marker levels (CEA, CYFRA21-1, SCC-Ag, NSE).

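### No TCM, quality-of-life or KPS score is scheduled at or after progression, so the 6-month TCM change tends to be missing in relation to the primary outcome; the likely between-arm bias is modest

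*Protocol article*

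**What the plan says.** **Endpoint.** Under Secondary outcomes, the TCM endpoint is "The absolute change in the total score from baseline to 6 months (D180 ± 7" days). The scale runs from 0 to 48, higher is worse, and the MCID is 4 points. Table 2 labels D180 the "Primary Time Point" for this score. Quality of life and KPS are listed as changes without a fixed time point.

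**Schedule.** In Table 2 the TCM score is marked at screening, D90 and D180. The rows beginning "Quality of life (EORTC QLQ" and "Performance status (KPS" are marked at those visits and at D365. The end-of-treatment column, headed "Upon PD/Discontinuation", is marked for confirmation of progression, tumour response, both laboratory rows, adverse events, dose modification and CRF completion. It is blank for all three instruments.

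**After treatment.** D90 and D180 are headed as treatment-period visits. Under TCM intervention, the granules "will continue until disease progression, unacceptable toxicity, or other criteria for treatment discontinuation are met". Under Withdrawal/termination criteria, participants who stop the intervention are "encouraged to continue in the follow-up phase for the collection of survival and safety data".

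**Analysis.** The TCM score and quality of life are analysed by MMRM (Comparative analyses). Missing continuous values are multiply imputed, with LOCF as the sensitivity analysis (Handling of missing data).

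**The concern.** Progression ends treatment, and a visit takes place at that moment, but the symptom scores are not taken there. Later scores are not provided for either. A patient who progresses before D90 may then have only a baseline score. One who progresses between D90 and D180 keeps the D90 score but may have no D180 value. Whether the D180 score exists thus depends on the primary outcome, and if YFXJD delays progression it depends on the arm as well.

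MMRM and multiple imputation under missing-at-random predict the absent value from arm, baseline and any D90 score, learning mostly from patients who stayed on treatment. LOCF carries forward a score taken before progression. If symptoms worsen at progression, none of the three sees it, so the sensitivity analysis shares the blind spot of the main one. What is at stake is the first-listed secondary endpoint and, with no fixed time point, the quality-of-life and KPS changes.

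**Working it through.** **Inputs from the article (Sample size):** control median PFS 18.9 months; HR 0.66; experimental median 28.6 months; 100 patients per arm. From Secondary outcomes: MCID 4 points. From Follow-up and assessments: imaging every 8 weeks.

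**Assumptions not in the article:** exponential PFS; no other dropout; 30.4375 days per month; progression adds 4 to 8 points (1 to 2 MCIDs) to the TCM score. The article gives no figure for that last quantity.

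**Step 1. The plan's own figure.** 18.9 / 0.66 = 28.64 months, which reproduces the stated 28.6.

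**Step 2. Share with a PFS event (progression or death) by day t:** 1 − exp(−ln 2 × t / median), with D90 = 2.96 months and D180 = 5.91 months.

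| By | Control (18.9) | YFXJD (28.6) | Patients of 200 |
|---|---|---|---|
| D90 | 10.3% | 6.9% | about 17 |
| D180 | 19.5% | 13.3% | about 33 |

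(The last YFXJD figure is 13.35% before rounding.) About 17 patients would have only a baseline score, and about 16 (33 − 17) would have D90 as their last score. With no treatment effect, both arms follow the control figure and the total is about 39.

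**Step 3. Allowing for scan dates.** Before D90 the only scheduled scan is at day 56; before D180 the last is at day 168. If the curve describes underlying progression times, the same formula at those days gives the share detectable on schedule:

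| Last scan | Control | YFXJD |
|---|---|---|
| Day 56 | 6.5% | 4.4% |
| Day 168 | 18.3% | 12.5% |

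Unscheduled scans and deaths would bring the numbers back towards step 2.

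**Step 4. Between-arm bias at D180,** taking the whole decline as unseen by the model:

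- 4 points: (0.195 − 0.133) × 4 = 0.25
- 8 points: (0.195 − 0.133) × 8 = 0.50

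With the day-168 shares: (0.183 − 0.125) × 4 to 8 = 0.23 to 0.46.

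**Direction.** Higher scores are worse, and more worsening goes unrecorded in control. The control mean looks better than it is by more than the YFXJD mean does, so benefit is understated. If HR = 1 the shares are equal and this difference is zero.

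**Within-arm mean change** is affected more: 0.195 × 4 to 8 = 0.8 to 1.6 points in control, and 0.133 × 4 to 8 = 0.5 to 1.1 in YFXJD.

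**The case against.** **The stop is inferred.** No sentence ends the D90 and D180 questionnaires at progression. Only imaging is limited to the time before progression, the 3-monthly visits carry no such limit, and progression is not among the withdrawal criteria. This stands. A reader might infer that the plan forbids later scores; it does not. But it does not schedule or request them either: it asks for follow-up "for the collection of survival and safety data, where feasible and with their consent".

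**Table 2 is not exhaustive.** The end-of-treatment blinding questionnaire and the 4-weekly ALT/AST tests have no matching entry, so a missing tick in a condensed article is weaker evidence. That is fair in general. Here, however, the three rows exist, are marked at other visits, and are blank in a column where neighbouring rows are marked.

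**The counts are high.** Scan timing lowers the early share (step 3), and the percentages include deaths, for whom no questionnaire can be completed. Both stand.

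**The effect is small.** It is 0.25 to 0.5 points against an MCID of 4, about 6% to 12% of it, on an assumed decline, for a secondary endpoint. That also stands.

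**The methods do not assume stability.** A reader might infer that MMRM and imputation treat progressed patients as unchanged. They condition on arm, baseline and any D90 score, and the unspecified imputation model could include progression status. What remains is that no observed score at progression exists from which to learn the size of the decline.

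**Scope.** Only the TCM score has a fixed 6-month endpoint, and KPS is not named among the MMRM variables. The argument about D180 therefore applies to the TCM score; for the other two the loss is of later scheduled values.

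**Conclusion.** The point holds as a gap in the schedule. As written, nothing provides for a TCM, quality-of-life or KPS score at or after progression. On the trial's own PFS assumptions, about 33 of 200 patients have a PFS event by D180, somewhat fewer as detected on scheduled scans. Their D180 TCM change tends to be missing for a reason tied to the primary outcome, with an imbalance of about 6 percentage points if the assumed effect is real.

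A reader might infer that the 6-month comparison is seriously biased, or biased in favour of YFXJD. The documents do not support either. The bias is about 0.25 to 0.5 points, rests on an assumed 4 to 8 point worsening, arises in this calculation only if YFXJD delays progression, and would tend to understate benefit. Discontinuation for toxicity can lose scores in the same way and is not in the count. The case for change is that the omission cannot be repaired after the event and is cheap to close now: 38 of 200 patients had been enrolled by July 2026.

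**What to change.** 1. In Table 2, mark the TCM syndrome score, QLQ-C30/LC13 and KPS at the end-of-treatment visit.
2. State that the D90 and D180 scores are still collected after progression or discontinuation where the patient consents, and align the Withdrawal/termination text, which now names only survival and safety data.
3. Use the end-of-treatment score, with its actual date and progression status, as predictors in the imputation model for D180. Do not relabel it as a D90 or D180 value: for a patient who progresses around day 56, that would put an off-window score at D90 and still leave D180 empty.

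These steps do not supply scores for patients who die before D180.

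**Cost:** one extra questionnaire set and ratings at a visit that already takes place, D90 and D180 scores for some off-treatment patients, and a schedule amendment with ethics approval. Patients who have already left treatment cannot be recovered for the end-of-treatment score.
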